## Abstract

**Background:**

Visual or visual-and-intellectual disabilities of children make daily interactions more difficult for their parents and may impact the quality of the parent-child relationship. To support these parents, an existing intervention (Video-feedback Intervention to promote Positive Parenting; VIPP; Juffer F, Bakermans-Kranenburg MJ, van IJzendoorn MH, 2008. Promoting positive parenting; an attachment-based intervention. Mahwah, NJ: Lawrence Erlbaum Associates; 2008) was adapted for use with parents of children with a visual or visual-and-intellectual disability (VIPP-V). This attachment-based intervention was hypothesized to support parents’ interpretation and understanding of the behavior of their child with a visual or visual-and-intellectual disability and respond to their child’s signals in a sensitive way to improve parent-child interaction quality.

**Methods/Design:**

A randomized controlled trial (RCT) will be conducted to assess the effectiveness of the adapted intervention VIPP-V (Video-feedback Intervention to promote Positive Parenting in parents of children with Visual or visual-and-intellectual disabilities). Parent-child dyads will be randomized into two groups: 50 dyads will receive VIPP-V in combination with care-as-usual and 50 dyads will receive care-as-usual. Families with a child (1–5 years of age) with a visual or visual-and-intellectual disability will be recruited for participation in the study. Primary outcome measures are parental sensitivity and the quality of parent-child interaction. Secondary outcome measures are parental self-efficacy, and parenting stress. To assess feasibility of implementation of the intervention the experiences of early intervention workers with regard to using VIPP-V are assessed. Moderator variables are the child’s developmental age, working alliance between parent and VIPP-V intervention worker and empathy of the VIPP-V intervention worker. Data will be collected approximately one week before the intervention starts (T1), one week (T2) and three months (T3) after the intervention. Parent-child dyads in the care-as-usual-only condition will be assessed at the same time points. Both intention-to-treat and completer analyses will be performed.

**Discussion:**

Descriptive findings in pilot cases suggest benefits from VIPP-V, and compatibility with existing services for parents of children with a visual or visual-and-intellectual disability. The current study will provide insight into the effectiveness of this intervention for parents of children with a visual or visual-and-intellectual disability, and, if the intervention is effective, prepare the field for broad-scale implementation.

**Trial registration:**

Nederlands Trial Register NTR4306 (registered 5 December 2013).

## Background

In general, for parents of children with a visual disability, mutual communication is more difficult than for parents with sighted children [1]. The attempts of children with visual disabilities to communicate with their parents are different and sometimes difficult to understand [2]. For example, parents may experience a feeling of rejection because of the lack of eye-contact, the absence of reciprocal smiling or the absence of gaze following as the parent moves around the room. Also, parents may experience their child to be unresponsive to their bids of attention because of the absence of facial expressions and emotional reactions [3]. In Western European countries about 50 % of children with visual disabilities also have an intellectual disability [4, 5]. For parents of children with a visual disability as well as an intellectual disability, interpretation of communication signals in their child may be even more difficult, because of the relatively slow speed at which the child processes (social) information and the delay in or absence of a reaction [1, 6]. These difficulties in understanding and interpreting their child’s behavior and interaction may cause parents to experience increased parenting stress, in turn reducing parental emotional availability, making parents less sensitive and responsive towards their child [1].

Diagnoses of the child’s visual or visual-and-intellectual disability may often come after a period of worry and uncertainty, because of the aberrant behavioral repertoire these children exhibit towards their parents [1]. Nevertheless, the actual diagnosis may often come as a shock, requiring parents to come to terms with possible feelings of sadness, disappointment and guilt [7]. This period around the diagnosis and the associated emotional upheaval coincides with an important period in infants’ lives; a period in which establishing close relationships with caregivers is an important, first developmental issue [8]. A secure attachment relationship provides an optimal basis for adaptive, resilient development [9], which may be particularly relevant for children with disabilities [10, 11].

Despite the fact that several studies have revealed difficulties for parents rearing their child with a visual or visual-and-intellectual disability [1, 3, 6], unfortunately so far little systematic attention has been given to the development of early intervention programs in which parents can learn to relate to their child with a disability in an appropriate and attuned way [2, 12]. Scientific insights on the importance of sensitive parenting and secure parent-child attachments for a positive social-emotional development have accumulated into a solid knowledge base for intervention, both for children with [13] and without disabilities [14]. For children without disabilities this has led to considerable progress in evidence-based intervention programs. A meta-analysis showed that particularly interventions focused on sensitive parenting were effective, even more so than interventions with a broad focus [15]. In addition, this meta-analysis showed that short-term interventions were more effective than long-term interventions (with more than 16 sessions). Based on these findings, Video-feedback Intervention to promote Positive Parenting has been developed (VIPP; [14]). VIPP is an evidence-based attachment-oriented intervention aimed to enhance parental sensitivity, by use of providing personal video-feedback on sensitive responsiveness [14]. This intervention has been adapted for and tested on effectiveness in several subpopulations: for example, parents of children with challenging behavior (VIPP-SD) [16], parents of children with autism (VIPP-AUTI) [17] and parents with a learning disability (VIPP-LD) [18].

In order to meet the needs of parents for support in improving the quality of the relationship with their young child with a visual or visual-and-intellectual disability, the existing Video-feedback Intervention to promote Positive Parenting (VIPP; [14]) has been adapted to Video-feedback Intervention to promote Positive Parenting in parents of children with Visual or visual-and-intellectual disabilities (VIPP-V). The original VIPP and elements of variations on VIPP for several subpopulations were used to tailor this new intervention to the specific needs of families with a young child with a visual or visual-and-intellectual disability. In VIPP-V parents are supported to show more sensitive responsive behavior towards their child by helping them to notice child signals, interpret them correctly, and respond to these signals promptly and appropriately [19]. Showing parents video-recordings of their own interaction with their child has been shown to enhance their insight in the specific needs of their child and improve parental responses [20]. In addition, parents are provided information on the effect of the visual disability on the behavior of their child.

### Trial objective

In the present study we will examine the effectiveness of an attachment-based video-feedback parenting intervention for parents of children with a visual or visual-and-intellectual disability (VIPP-V) by use of a randomized controlled trial (RCT) with two groups: one group will receive VIPP-V in combination with care-as-usual and one group will receive care-as-usual only. Effectiveness is measured in terms of improved parental sensitivity, parent-child interaction quality, parental self-efficacy and decreased parenting stress. Potential moderating variables will be investigated in order to identify predictors of effectiveness. A secondary goal of the study is to assess the feasibility of implementing VIPP-V in regular care and prepare the field for broad-scale implementation if the new intervention is effective.

### Hypotheses

The main hypotheses to be tested are:Participation in VIPP-V will be associated with stronger improvement in parental sensitive responsiveness and quality of parent-child interaction than receiving care-as-usual only.Parents participating in VIPP-V will show a stronger increase in parental self-efficacy and a stronger decrease in parenting stress than parents receiving care-as-usual only.

## Methods

### Study design

This study is a multicenter RCT with pretest, post-test assessments and follow-up after three months (three time points), including two groups: an experimental group who will receive VIPP-V in combination with care-as-usual, and a control group who will only receive care-as-usual. Randomization will be performed as stratified block randomization with a 1:1 allocation. This trial will be carried out in two national organizations specialized in care for people with visual disabilities and their families (Royal Dutch Visio and Bartiméus). These organizations have offered services to people with visual disabilities and their families since the 1980s and have multiple rehabilitation centers all over The Netherlands. Together, Royal Dutch Visio and Bartiméus provide care for the majority of families eligible for participation in the study (with the exception of families living in the three northern-most counties because of organizational issues).

### Study population

One hundred families with a child (aged 1–5 years) with a visual or visual-and-intellectual disability will be recruited from the population of families receiving early intervention services from Royal Dutch Visio and Bartiméus. For about a quarter of all families receiving care from these organizations, it is very likely that the child also has an intellectual disability. These children will also be included in the study, because at this young age it is often difficult to distinguish an intellectual disability from cognitive slow development and the expectation is that parental sensitivity is equally important for children with and without an intellectual disability.

### Inclusion and exclusion criteria

Families with a child with a visual or visual-and-intellectual disability, aged between 1 and 5 years, who are willing to take part in a video-feedback intervention are eligible for participation in the study. All included children will have a visual disability, as defined according to the World Health Organization (WHO) standards [21]. For children with a learning disability, a clinical psychologist must assess this. Written consent for participation in the study needs to be given by either a parent or, if both parents have custody over the child, by both parents. Parents with visual or auditory disabilities themselves can also participate in the study as extra case studies (in addition to the 100 families that are planned to be included), as it is not yet known how these parents can benefit from the use of video-feedback. Excluded from participation in the study are: families with a child with a developmental age below nine months, because the attachment relationship may not be stable before that age; families with a child who does not live at home: for example due to hospitalization for serious medical problems; parents with an intellectual disability; and multiple children from the same family.

### Interventions

#### Video-feedback Intervention to promote Positive Parenting in parents of children with Visual or visual-and-intellectual disabilities (VIPP-V)

In a collaborative project together with Royal Dutch Visio and Bartiméus, the intervention program Video-feedback Intervention to promote Positive Parenting in parents of children with Visual or visual-and-intellectual disabilities (VIPP-V), was developed. This intervention program was based on the original VIPP [14] and elements of VIPP-SD [16] and VIPP-AUTI [17] were used to make this new intervention applicable for use with families with a young child with a visual or visual-and-intellectual disability. Adaptations were made based on knowledge of the behavior patterns of young children with visual or visual-and-intellectual disabilities, together with clinical experience and knowledge of attachment-based interventions. VIPP-V consists of seven 1.5 hour-sessions. The first five sessions are spent on the original VIPP themes (Attachment and exploration; “Speaking for the child”; Chain of sensitivity; and Sharing of emotions) with an added component related to visual or visual-and-intellectual disabilities each session. The sixth and seventh sessions are booster sessions. The added themes for parents of children with visual or visual-and-intellectual disabilities are: 1) predictability and safety; 2) independence, making demands of the child, and dealing with change and frustration; 3) sharing of attention and joint attention; 4) recognizing and naming emotions and empathy and induction. These added themes focus on skills which (parents of) children with visual or visual-and-intellectual disabilities often have difficulties with. An overview of the themes of the different home-visits can be found in Table 1. The intervention focuses on the primary caregiving parent. The five regular home-visits are scheduled every 2–3 weeks, and the two booster sessions are scheduled in the next two months (every 4–5 weeks). In these booster sessions the other parent is also invited to participate.

**Table 1 Tab1:** Description of themes in each home-visit in VIPP-V, including additions to the original VIPP

	Themes of VIPP	Additions in VIPP-V
Home-visit 1	Only used for video-taping parent-child interaction. Discussion of interaction starts at home-visit 2	No additions
Home-visit 2	*Exploration	*Predictability
	*Proximity-seeking	*Safety
Home-visit 3	“Speaking for the child”	*Independence
		*Making demands of the child
		*Dealing with change and frustrations
Home-visit 4	*Sensitive responsiveness to child’s signals	*Sharing of attention
	*Chain of sensitivity	*Joint attention
Home-visit 5	*Sharing of emotions	*Recognizing and naming emotions
	*Chain of sensitivity	*Empathy and induction
	*Corrective messages	
Home-visits 6 and 7 (booster sessions)	Repetition	Repetition

For every home-visit VIPP-V intervention workers will use a protocol in which the goals and activities of the home-visit are described. By use of a protocol the intervention is standardized, but the protocol leaves enough flexibility to tailor the intervention to the characteristics and needs of each specific parent-child dyad. Every home-visit starts with video-taping the participating parent and child engaging in several tasks (for example playing together, teaching the child a task). After every home-visit the VIPP-V intervention worker prepares feedback on the video-taped interactions. This feedback is discussed in the next home-visit, directly after video-taping new material for the home-visit thereafter. Besides feedback the intervention worker also provides information and tips regarding sensitive responsiveness and visual or visual-and-intellectual disabilities. At the end of the intervention, parents receive a brochure with a summary of the most important elements discussed in intervention, including several tips, and a USB-stick with the video-recordings.

Leiden University and VU University Amsterdam have extensive experience in training professionals in VIPP and maintaining treatment fidelity through regular supervision, both within and between universities. Researchers of Leiden University have trained eight special education and behavioral experts from Royal Dutch Visio and Bartiméus as coaches in VIPP in a five-day training. During this training period all eight coaches practiced their newly acquired skills in a pilot family, and received five intervision sessions of 3 hours each with fellow coaches and three supervision session of 3.5 hours each. At the end of the training period trainers from Leiden University checked and approved the video-recordings and scripts of one of the seven home-visits of all coaches. Then, two of these coaches (one of each organization), in alternating collaboration with the second author, have trained fifteen early intervention workers in conducting VIPP-V. Early intervention workers received five days of training in VIPP-V over a period of two months. During this same period the intervention workers completed a VIPP-V intervention with families who, due to age, could not be included as participants in the study. Each of the five training days was dedicated to one home-visit (the last two of the seven sessions are booster sessions in which previous topics are repeated), and during the training all intervention workers participated in intervision sessions on each VIPP-V home-visit. Two of the trainers provided feedback on one of the scripts and on a video-recording of the feedback moment with the parent of each intervention worker. The VIPP-V training materials, video-recordings, scripts and provided feedback of the trainers of all intervention workers were finally sent to researchers of Leiden University for a check, and approved. These 23 VIPP-V intervention workers will provide VIPP-V to the different participating families. In addition, the eight VIPP-V coaches will participate in three supervision meetings with the fifteen early intervention workers during each VIPP-V trajectory.

#### Care-as-usual

Families randomized into the experimental condition will receive both VIPP-V and care-as-usual, while families randomized into the control condition will receive only care-as-usual. At Royal Dutch Visio and Bartiméus families receive care for a wide range of issues and topics, such as mobility training and magnifier training for the child, and guidance for parents on parenting issues, play behavior and choice of schools. At pretest, post-test and follow-up all families are asked about the kind and amount of care they have received recently. An analysis and comparison will be made of the received care-as-usual in both conditions. If necessary, kind and amount of care-as-usual will be controlled for in analyses.

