### Randomization

Randomization will be done by use of a computerized random number generator by the first author. Using stratified randomization, equal randomization of families from both Royal Dutch Visio and Bartiméus will be achieved, as well as equal representation of children with varying chronological ages. Stratified randomization reduces the risk for baseline imbalance between conditions [44]. For each organization separately, the random allocation list will be generated in three blocks with a 1:1 allocation, based on three periods in which the intervention will be offered. After the second block a check will be done for baseline imbalances between conditions, so, if necessary, these imbalances can be corrected in the final block. Each block will be randomized roughly three weeks before the start of the intervention. The numbers on the list will be paired with the participating families in order of the date on which informed consent is obtained.

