### Blinding

Parents agree to participate in the study before randomization and without knowing in which condition they will participate. The condition in which parents will participate will be disclosed to them directly after randomization of the block they belong to (roughly three weeks before the start of the intervention). Every ID-number assigned to families is independent of condition. Researchers coding and analyzing the observation data will be blind to the condition of parents and children, as well as the assessment (pretest, post-test, follow-up). Research assistants conducting the assessments are not blinded to the condition or assessment, because different questionnaires are used for families participating in the intervention condition and in the control condition (families in the control condition are not asked about working alliance of the VIPP-V intervention worker) and per assessment. Intervention workers are, necessarily, not blind to randomization allocation.

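### Usual care may be controlled for without limiting this to care received before allocation, which could bias the intention-to-treat effect in either direction

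*Protocol article*

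**What the plan says.** The Care-as-usual section of the protocol article sets out three steps.

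- Measurement: "At pretest, post-test and follow-up all families are asked about the kind and amount of care they have received recently".
- Comparison: "An analysis and comparison will be made of the received care-as-usual in both conditions".
- Adjustment: "If necessary, kind and amount of care-as-usual will be controlled for in analyses".

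The article does not define when adjustment is necessary, which assessment's care would enter the model, or which analyses are meant. It does not say that the unadjusted comparison stays primary.

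The Trial objective section gives the contrast of interest: "one group will receive VIPP-V in combination with care-as-usual and one group will receive care-as-usual only". The Drop-outs and Data analysis sections commit to intention-to-treat analysis, with a completer analysis alongside it.

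**The concern.** The randomised contrast covers everything that follows from allocation, including any change in the usual care a family goes on to receive. Three features of this trial make such a change plausible.

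- Usual care includes "guidance for parents on parenting issues, play behavior and choice of schools". The first two overlap with what VIPP-V works on, so home visits could take the place of some of that guidance.
- Control families had to be willing to take part in a video-feedback intervention to be eligible. They then learn that they will not receive it, and they may look for other support.
- The same two organisations supply the VIPP-V workers and the usual care, so one service can readily be traded against the other.

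The amount of care may also reflect how the family is doing, and so share causes with parental sensitivity. Conditioning on T2 or T3 care would then do two things. It would remove whatever part of the effect runs through usual care, and it would bring in confounding between care and outcome. The adjusted difference would no longer estimate the contrast in the Trial objective section. The decision to adjust would also follow a look at data gathered after randomisation.

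**Working it through.** **Order of events**

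1. Randomisation: "Each block will be randomized roughly three weeks before the start of the intervention".
2. Disclosure: "The condition in which parents will participate will be disclosed to them directly after randomization of the block they belong to".
3. Assessments: "Data will be collected approximately one week before the intervention starts (T1), one week (T2) and three months (T3) after the intervention".

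T1 therefore falls about 3 − 1 = 2 weeks after randomisation, with allocation already known to the family. All three care reports come after disclosure, and T2 and T3 also come after VIPP-V has been delivered. At T1 the question about recent care may still reach back before randomisation, so T1 care is less exposed than T2 or T3 care, but it is not strictly a baseline measure.

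**The plan's own figures**

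The Sample size calculation section gives f = 0.17 (d = 0.33), alpha 0.05, power 0.97 with 100 families and 0.80 with 58. For the group-by-time interaction with two groups and m = 3 assessments, λ = f²·N·m/(1 − ρ), with 2 and 2(N − 2) degrees of freedom. The article gives no correlation, so ρ = 0.5 and sphericity are assumed.

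- N = 100: λ = 0.0289 × 100 × 3 / 0.5 = 17.34; power 0.967.
- N = 58: λ = 0.0289 × 58 × 3 / 0.5 = 10.06; power 0.807.

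Both figures reproduce, and this point changes neither. The issue is what the adjusted model estimates.

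**How far adjustment could move the estimate**

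The documents give no figure for differences in usual care, so every input below except 0.33 is an assumption. Let a be the effect of allocation on usual care (SD), b the effect of usual care on the outcome (SD per SD), and u the loading of an unmeasured family factor on both care and outcome. In a linear model with unit variances:

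adjusted effect = total effect − a·(b + u²)

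With no shared cause (u = 0), the shift is a·b. It runs from 0.3 × 0.1 = 0.03 SD to 0.5 × 0.3 = 0.15 SD. With a total effect of 0.33:

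| a | b | u | Calculation | Adjusted effect |
|---|---|---|---|---|
| 0 | any | any | 0.33 − 0 | 0.33 |
| +0.3 | 0.2 | 0 | 0.33 − 0.06 | 0.27 |
| +0.5 | 0.3 | 0 | 0.33 − 0.15 | 0.18 |
| −0.5 | 0.3 | 0 | 0.33 + 0.15 | 0.48 |
| +0.5 | 0 | 0.4 | 0.33 − 0.08 | 0.25 |
| −0.5 | 0 | 0.4 | 0.33 + 0.08 | 0.41 |
| +0.5 | 0.3 | 0.4 | 0.33 − 0.23 | 0.10 |
| −0.5 | 0.3 | 0.4 | 0.33 + 0.23 | 0.56 |

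Simulation of 4,000 trials of 100 families per setting agreed for the rows with non-zero a (for example 0.181, 0.478, 0.101 and 0.564 for rows 3, 4, 7 and 8). The unadjusted estimate stayed near 0.33 throughout. A negative a, where VIPP-V displaces usual care, inflates the adjusted effect. A positive a shrinks it.

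**Can a caused difference be told from a chance one?**

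With 50 families per arm, unit SD and no clustering, the standard error of the arm difference in care is √(1/50 + 1/50) = 0.20 SD. An observed difference of 0.3 SD is then 1.5 standard errors, so it could be chance or a real effect of allocation. Comparing the arms does not settle whether adjustment is safe.

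**The case against.** The best defence is that the sentence is a contingent remark in the description of the interventions. The Data analysis section does not repeat it; the only covariate adjustment named there for the outcome comparison is for baseline differences. The section on control variables lists stressful experiences and treatment integrity, not usual care. The article also presents VIPP-V as an addition to usual care, and much of that care (mobility training, magnifier training, school choice) has no evident reason to change with allocation. Details of the model may lie in a fuller document.

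Much of this stands, and it rules out some stronger readings that a reader might infer:

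- That T2 and T3 care is a consequence of allocation. The documents show that it can be, not that it is.
- That adjustment is triggered exactly when the arms differ. This is the natural reading after the comparison sentence, and it matches the rule for baseline differences, but the article does not say so.
- That an adjusted estimate will replace the unadjusted one. The article neither says this nor excludes it.

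What the defence does not remove is the stated permission itself. Nothing in the article limits it to care received before allocation, keeps it out of the main outcome models, or protects the unadjusted contrast. That goes beyond missing detail, because following the sentence as written can give a biased answer to the trial's own question. Measuring usual care and comparing it by arm is good practice and is not in dispute.

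**Conclusion.** The point holds in conditional form. The article allows the outcome comparison to be adjusted for usual care reported after randomisation. If allocation changes that care, the adjusted estimate could be biased for the intention-to-treat effect, upwards or downwards. If allocation leaves care unchanged, no such bias arises.

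The size is unknown from the documents. Under the assumed inputs with no shared cause, the shift is 0.03 to 0.15 SD against a planned d of 0.33. A reader might turn this into a loss of 9% to 45% of the effect (0.03/0.33 and 0.15/0.33). Those percentages are only the assumptions divided by 0.33; they do not show a likely size, and the shift need not be a loss. No stated figure in the protocol is wrong.

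The sentence should be changed, because the risk falls on the primary comparison and is cheap to remove.

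**What to change.** Replace the adjustment sentence in the Care-as-usual section with wording to this effect:

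- Usual care at T1, T2 and T3 is reported by arm, to describe the treatment contrast actually delivered.
- Usual care reported at T2 and T3 does not enter the models for the primary and secondary outcomes.
- Only care received before randomisation may be a covariate, and only if prespecified. Because T1 follows randomisation and disclosure, the T1 question must refer to the period before allocation.
- Any model that includes later care is labelled exploratory or mediation analysis and is reported beside the intention-to-treat comparison, not in place of it.

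The cost is a few lines of analysis wording and, where T1 care is to serve as a covariate, a defined reference period for that question. No additional assessment is needed. Data collection was in progress when the article was written. If T1 answers already collected cannot be tied to the period before allocation, T1 care should be left out of the outcome models as well.
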